**Figure 2 figure2:**
[figure not shown]
Sample size calculations.

### Statistical Analysis

Analysis will be done on an intention-to-treat basis. Given the possibility of a proportion of crossovers, a secondary sensitivity per-protocol analysis will be undertaken. The statistical analysis for the primary outcome measure will be done in a noninferiority design with 95% CI and a noninferiority margin of 3.5% between the groups, while the secondary measures will be analyzed in a superiority design, where a *P* value of less than .05 is considered statistically significant.

Patient data will be prospectively collected and registered on case report forms. Age; sex; date of trauma; blood thinners; medical history; GCS and neurological condition at admission; hematoma size; side; and the existence of brain herniation, hydrocephalus, and midline shift are documented as basic characteristics. Clinical outcome variables (24 hours postoperative, at discharge, 6 weeks postoperative, and 12 months postoperative): Glasgow Coma Scale and (improvement of) neurological condition, mRS, Glasgow Outcome Score, Markwalder score, recurrence needing reoperation, complications (eg, infection, epilepsy, aphasia, paresis), hospitalization time, and mortality. Radiological outcome variables (24 hours postoperative and 6 weeks postoperative): hematoma size, midline shift, and rebleed seen on cranial CT. Intraoperative variables: elective or emergency procedure, type of hematoma (chronic, acute, subacute), drain type, crossover, number of membranes, and existing communication between the two burr-holes.

### Monitoring

The trial master folder and case report form data for each participant will be inspected by a monitor at yearly intervals throughout the study to verify the completeness, consistency, and accuracy of the data. The existence and integrity of the informed consent forms signed by the patient or legal representative will be monitored as well. The study monitoring is provided by Kammermann Monitoring Service, Zug, Switzerland.

A strict confidential yearly interim analysis is done by a statistician (Clinical Trial Unit, Basel, Switzerland) for the recurrence rate (primary outcome measure) and morbidity (secondary outcome measure). The trial will be stopped if the intervention arm (SPD) shows a significant noninferiority margin of 3.5% compared to the treatment arm (SDD) or if recruitment rates are unexpectedly low.

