**Results:**

This research is investigator-initiated and has received ethics approval. Patient recruitment started in April 2013, and we expect all study-related activities to be completed by the end of 2016 or beginning of 2017.

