### Sample Size

Initially the study was planned as a superiority study to show a significant difference in the recurrence rate of cSDH between insertion of an SPD and an SDD. When estimating the sample size, a difference in the recurrence rate of 10% in the SDD group versus 20% in the SDP group was assumed (based on Bellut et al and Santarius et al [2,5]), leading to the estimate of 150 patients in each group. New studies [12] and the blind data review of the first 56 patients (both groups pooled) suggested a lower recurrence rate of 7%. Therefore the sample size was reviewed. At the same time, the study design was changed from a superiority to a noninferiority design, and a noninferiority margin of 3.5% was defined.

We reestimated the recurrence rates in a blinded manner based on the overall recurrence rate. Since no hypothesis test was performed, no *P* value adjustment to control type I error was needed. Data from all patients who had a follow-up visit could be used for the sample size review. When reestimating the recurrence rates, it was assumed that the probability of being in one group or the other (SDD vs SPD) for patients who had a follow-up visit would be equal. As stated the reestimated recurrence rate was 7%, which was the expected difference between the SDD group and SPD group (3.5%−10.5%=7%). Using the reestimated recurrence rates, the sample size N was reestimated using a resampling procedure. Each sample size, N_i=1;...;101_=50;...;150, was evaluated by sampling 9999 times N_i_ individual samples based on the assumptions described above. Confidence intervals (CIs) for the difference between proportions were calculated using a continuity-corrected modification of the Wilson score method. Sample size was set to ensure with 80% power (1–β=0.8) (ie, in 80 of 100 hypothetical repetitions of the study) the estimation of a 95% CI, which is entirely below the predefined noninferiority margin of 3.5%.

For this study, a total of 220 patients should be randomized to ensure 208 evaluable patients (110 patients randomized per study arm) (Figure 2) considering an overall drop-out rate of 5% after randomization (eg, death, lost to follow-up).

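### The interim stopping sentence can be read as two opposite rules; if it means stopping for noninferiority, the yearly looks as written carry no type I error control

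*Protocol article*

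**What the plan says.** All references are to the protocol article.

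- **Monitoring**, on interim analysis: "A strict confidential yearly interim analysis is done by a statistician", covering the recurrence rate (primary outcome) and morbidity. The stopping sentence follows: "The trial will be stopped if the intervention arm (SPD) shows a significant noninferiority margin of 3.5% compared to the treatment arm (SDD"). Unexpectedly low recruitment is the only other ground for stopping. The number of looks, their timing, a boundary and a level are not given.
- **Statistical Analysis**: the primary outcome is analysed in a "noninferiority design with 95% CI and a noninferiority margin of 3.5% between the groups".
- **Sample Size**: the planning criterion is "the estimation of a 95% CI, which is entirely below the predefined noninferiority margin of 3.5"%. The interval is a continuity-corrected Wilson score interval for the difference in proportions. The section says no adjustment for type I error was needed, and ties this to the blinded review, in which nothing was tested.
- **Trial Design** makes SPD the intervention arm and SDD the control arm. The stopping sentence calls SDD the treatment arm.
- **Abstract, Results**, on the timeline: "Patient recruitment started in April 2013, and we expect all study-related activities to be completed by the end of 2016" or early 2017.

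**The concern.** A significant noninferiority margin is not a test result. A statistician applying the sentence must choose between two rules:

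- **Reading A:** stop when the CI shows SPD to be noninferior. This is early stopping for success.
- **Reading B:** stop when SPD is significantly worse, by the margin. This is stopping for harm or failure.

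The mislabelled SDD arm adds to the doubt. Under A, recurrence has no stopping rule for SPD doing worse. Under B, nothing says what level counts as significant.

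Under A there is a second problem. The rule compares the arms on the primary outcome every year and stops on a significant result, while the final analysis still spends the whole one-sided 2.5%. The type I error remark under Sample Size cannot cover this, since its ground is that no test was done. The trial's one confirmatory claim is noninferiority, so the error at stake is declaring noninferior a drain that is worse by the margin. A stop at an interim would also shrink the complication and mortality comparisons that form the secondary objective.

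**Working it through.** **Inputs from the article.** Margin 3.5 points; two-sided 95% CI (one-sided 2.5%); 1:1 allocation; 208 evaluable patients, so 104 per arm; 12-month endpoint. Planning rates are 3.5% and 10.5%. Only SPD 3.5% and SDD 10.5% reproduces the stated power. The opposite assignment, which the order of words in "which was the expected difference between the SDD group and SPD group (3.5%−10.5%=7"%) would suggest, gives about 0.07%.

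**Assumption on looks.** Yearly looks between April 2013 and the end of 2016 or early 2017 allow up to three interims plus the final. If 12-month outcomes are required, the first of these would have almost no data, leaving about two informative interims plus the final. Equal spacing is assumed: 35/69/104 or 26/52/78/104 per arm.

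**Test.** Noninferiority is declared if U < 0.035, where

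U = (p₁ − p₂) + √[(u₁ − p₁)² + (p₂ − l₂)²],

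with 1 = SPD, 2 = SDD, and u, l the continuity-corrected Wilson limits:

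- l = [2np + z² − 1 − z√(z² − 2 − 1/n + 4p(nq + 1))] / [2(n + z²)]
- u = [2np + z² + 1 + z√(z² + 2 − 1/n + 4p(nq − 1))] / [2(n + z²)]

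with q = 1 − p and z = 1.96.

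**Step 1: the plan's own figure.** Exact binomial enumeration at SPD 3.5%, SDD 10.5% and 104 per arm gives power of 78.5% (84.5% without the continuity correction). At 110 per arm the corrected figure is 82.6%. The stated 80% is reproduced to within 2 points. For dropout, 208 / 0.95 = 219, against 220 stated.

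**Step 2: false noninferiority under Reading A.** The true difference is set at the margin (SPD = SDD + 3.5 points). The entry is the probability that U < 0.035 at any look, from 400,000 simulated trials per scenario. The normal-theory row uses 2 million paths.

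| Interval | SDD rate | Single look | 2 interims + final | 3 interims + final |
|---|---|---|---|---|
| Corrected Wilson | 3.5% | 1.15% | 1.74% | 1.75% |
| Corrected Wilson | 7% | 1.46% | 2.67% | 2.74% |
| Corrected Wilson | 10.5% | 1.70% | 3.23% | 3.49% |
| Uncorrected score | 3.5% | 2.1–2.2% | 3.75% | 4.15% |
| Uncorrected score | 7% | 2.3–2.4% | 4.80% | 5.66% |
| Uncorrected score | 10.5% | 2.4% | 4.99% | 6.06% |
| Normal theory | – | 2.5% | 5.4% | 6.3% |

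Ratios to the single look run from 1.74 / 1.15 = 1.5 to 6.06 / 2.41 = 2.5. Under the corrected interval they are 1.5 (SDD 3.5%), 1.8 to 1.9 (7%) and 1.9 to 2.1 (10.5%).

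**Step 3: Reading B.** A stop because SPD is worse never declares noninferiority, so it cannot add to the false noninferiority rate.

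**Step 4: bounds that would restore control.** O'Brien-Fleming at four equal looks has z_k = 2.022 × √(4/k), which gives about 4.04, 2.86, 2.34 and 2.02. The one-sided levels are 0.00003, 0.0021, 0.0098 and 0.0216. The final CI level is 1 − 2 × 0.0216 = 95.7%. With three looks the levels are 0.00026, 0.0070 and 0.0225, and the final CI is 95.5%.

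**The case against.** - **Two readings, one inflation.** The readings are alternatives, and only A inflates the error. This stands. The inflation cannot be stated as a plain fact about the trial.
- **The interval named in the article is conservative.** With it, four unadjusted looks give about 2.7% to 2.8% at SDD 7% and 1.8% at SDD 3.5%. One interim at 60 per arm plus the final gives 2.2% at SDD 7%. This also stands. A reader might infer that the false noninferiority rate is about 5% to 6%, but that needs an uncorrected interval or normal theory. Statistical Analysis does not name the analysis interval, so neither case can be ruled out. The excess at SDD 10.5% (3.2% to 3.5%) remains even with the corrected interval.
- **Boundaries may sit in a fuller document.** A condensed article may leave nominal levels to the full protocol or an interim charter, and their absence alone would be no finding. But the article itself states the trigger and the threshold, and it keeps a full 95% CI at the end. As written, the two do not fit together under Reading A. This does not prove that no adjustment exists elsewhere.
- **Early stops on few patients with short follow-up.** A reader might infer this, but the article does not say that incomplete follow-up would count at a look. With the corrected interval only about 7% of trials at the planning values stop at 26 per arm. About 65% do stop before the final analysis (75% uncorrected), but SPD is then truly 7 points better, so those stops are correct conclusions.

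**Conclusion.** The stopping sentence needs correction on either reading, because it cannot be applied without guessing its direction. That part rests on the text alone.

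The type I error part is conditional on three things: that the rule means stopping for noninferiority, that there are two to three interims plus a final analysis at roughly equal spacing, and that each look uses the ordinary 95% CI. Given these, the false noninferiority rate rises about 1.5 to 2.5 times over a single look. The overall one-sided rate is about 1.7% to 3.5% with the corrected interval, which is under 2.5% at SDD 3.5% and above it at 7% and 10.5%. It is about 3.8% to 6.1% with an uncorrected score interval. The documents do not support an unconditional claim that the error rate is doubled. If the rule means stopping because SPD is worse, there is no inflation and the defect is the missing level.

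**What to change.** 1. **Rewrite the stopping sentence so that its direction is explicit**, in terms of a CI limit for SPD minus SDD: the upper limit below 3.5 points for a noninferiority stop, or the lower limit above a stated value for a stop because SPD is worse. Call SDD the control arm. If both stops are intended, give each its own sentence and level.
2. **If noninferiority stopping was not intended or is not needed, remove it.** The final 95% CI can then stay. The cost is the chance to end early.
3. **If it is kept, state the number of looks and group-sequential bounds**, for example the O'Brien-Fleming levels above. Report the final CI at the matching level (95.7% for four looks, 95.5% for three), and base each look on patients with a complete 12-month outcome.
4. **Name the CI method for the analysis**, since the size of the problem depends on it.

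The text change is one paragraph. With O'Brien-Fleming bounds at four looks, power at the planning values falls from about 78.5% to 76.9% with the corrected interval (1.6 points), or from 84.4% to 82.6% uncorrected (1.8 points). The sample size statement, "Sample size was set to ensure with 80% power", should be restated to match.

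### The interim stopping sentence is unclear in direction: on its natural reading no between-arm trigger covers SPD doing worse, and on either reading the yearly morbidity comparison has no stated consequence.

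*Protocol article*

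**What the plan says.** Monitoring: "A strict confidential yearly interim analysis is done by a statistician" "for the recurrence rate (primary outcome measure) and morbidity (secondary outcome measure"). Two stopping triggers follow. One is between the arms: "The trial will be stopped if the intervention arm (SPD) shows a significant noninferiority margin of 3.5% compared to the treatment arm (SDD"). The other concerns feasibility: "or if recruitment rates are unexpectedly low".

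Sample Size: the trial began as a superiority study in which "a difference in the recurrence rate of 10% in the SDD group versus 20% in the SDP group was assumed". After new studies and a blinded review giving a pooled rate of 7%, it was changed to noninferiority and "a noninferiority margin of 3.5% was defined". The re-estimated rates are given as the 7% "which was the expected difference between the SDD group and SPD group (3.5%−10.5%=7"%).

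Serious Adverse Events: deaths, new hospitalizations, recurrent events and lasting disability caused by the surgery, among others, are reported to the ethics committee within 7 days.

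**The concern.** The sentence governs what happens to the trial after each yearly look, so its direction matters. An arm does not show a margin, and two readings are possible:

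- **Noninferiority has been shown.** This is the natural reading. The only between-arm action is then to stop when SPD succeeds, and a look at which SPD is clearly worse on recurrence leads to no stated action.
- **SPD exceeds SDD by more than 3.5%.** The rule is then a recurrence harm stop and there is no success stop.

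On both readings morbidity is compared every year with no consequence stated. Two statisticians could act in opposite ways on the same interim table. In a noninferiority trial the main reason to look early by arm is to protect patients from an inferior arm, and on the natural reading the written rule does not do this.

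**Working it through.** **Inputs.** From the article: 3.5% margin; 95% CI for the difference in proportions from a continuity-corrected Wilson method; 208 evaluable patients, so 104 per arm; rates of 3.5% and 10.5%; pooled rate 7%; superseded rates SDD 10%, SPD 20%. Assumed: the looks. The article states neither their number nor their size. Enrollment from April 2013 and completion around the end of 2016 leave room for two or three yearly looks. With a 12-month endpoint the first may hold few complete patients. Four schedules were therefore used, in patients per arm: 10 and 40; 20 and 60; 35 and 70; 26, 52 and 78.

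**Interval.** For x events in n, with p = x/n and z = 1.96:

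l = [2np + z² − 1 − z√(z² − 2 − 1/n + 4p(n(1−p)+1))] / [2(n+z²)]

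u = [2np + z² + 1 + z√(z² + 2 − 1/n + 4p(n(1−p)−1))] / [2(n+z²)]

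With 1 = SPD and 2 = SDD, the lower limit of the difference is (p1−p2) − √[(p1−l1)² + (u2−p2)²] and the upper is (p1−p2) + √[(u1−p1)² + (p2−l2)²].

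**Plan's own figure first.** Exact binomial enumeration at 104 per arm, SPD 3.5% v SDD 10.5%, success if the upper limit is below 3.5%: power 78.5%, against the stated 80% (82.6% at 110 per arm). The interval is therefore close to the one planned. This works only with SPD as the better arm. In the order printed (SDD first), the chance of showing noninferiority is 0.07%.

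**Harm check: lower limit above 0.** Example at 70 per arm, SPD 14/70 and SDD 5/70: p1 = 0.2000, l1 = 0.1174, p2 = 0.0714, u2 = 0.1657. Lower limit = 0.1286 − √(0.0826² + 0.0942²) = 0.1286 − 0.1253 = 0.003, so the check fires.

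Simulated chance that it fires at any interim look:

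| Looks per arm | SPD 10.5% v SDD 3.5% | SPD 20% v SDD 10% (superseded) | 7% v 7% |
|---|---|---|---|
| 10, 40 | 8% | 17% | 0.5% |
| 20, 60 | 18% | 27% | 0.9% |
| 35, 70 | 25% | 33% | 1.2% |
| 26, 52, 78 | 31% | 40% | 1.6% |

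**The written rule in the same settings** (schedules 35, 70 and 26, 52, 78). Read as a success stop, it fires in about 0.1% of trials at SPD 10.5% v SDD 3.5% and about 0.2% at 20% v 10%. Read as a harm stop, taken as the whole CI above +3.5%, it fires in 7% to 8% and 16% to 19%.

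**Effect on the primary conclusion.** A harm referral can only remove noninferiority conclusions, never add one, so the false noninferiority rate cannot rise. Under SPD 3.5% v SDD 10.5% the check fires in about 0.01% of trials or fewer, and final power is about 78% with or without it.

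**Unneeded referrals with equal arms, looks at 35 and 70.** The article gives no morbidity or mortality rates, so these are assumed, and endpoints are treated as independent. The chance per endpoint is 1.2% for recurrence at 7%; 1.7% and 2.9% for morbidity at 10% and 30%.

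- Recurrence plus morbidity (deaths counted within it): 1 − 0.988 × 0.983 = 2.9%, to 1 − 0.988 × 0.971 = 4.1%.
- Deaths tested separately as well, at 5% (0.75%) or 15% (2.3%): 1 − 0.988 × 0.983 × 0.9925 = 3.6%, to 1 − 0.988 × 0.971 × 0.977 = 6.3% (6.2% unrounded).

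**The case against.** The strongest reply is that the certain defect is unclear wording, and one-directionality is only an inference from it. That stands: a reader might conclude that the trial can stop only for SPD success, but the sentence can be read as a recurrence harm rule, and the two triggers are not said to be exhaustive.

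A condensed article may also leave safety guidance to the full protocol. This stands in part. Silence alone would be no finding, but here the article states its stopping rule, and states it badly.

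A reader might also infer that patients have no protection from harm. The documents do not support that. Serious adverse events, including deaths and recurrent events, go to the ethics committee individually, and morbidity is looked at every year. Case-by-case reporting is nevertheless not a comparison between arms.

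Nor does the article support the inference that the current plan expects SPD recurrence to be double. The 20% v 10% assumption was replaced, and the Introduction describes SPD as the presumed safer drain with no recurrence difference in earlier comparisons. It shows only that an SPD excess was once thought plausible.

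Finally, the frequencies depend on assumed looks, and the check misses most trials even at doubled recurrence. Both are true, so a range is shown and the proposal is a guideline for referral rather than a stopping boundary.

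**Conclusion.** The concern holds in this form: the stopping sentence does not fix its direction; on its natural reading there is no between-arm trigger for SPD being worse; and on either reading morbidity has no stated consequence. It is worth correcting because the comparison is already produced yearly.

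The size depends on unstated look times. A recurrence check would refer about 8% to 31% of trials at SPD 10.5% v SDD 3.5%, and 17% to 40% at the superseded rates. These are referrals for a decision, not stopped trials. A fuller protocol or monitoring charter may already hold such a guideline; if so, the article's sentence needs only to be aligned with it.

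**What to change.** 1. Rewrite the sentence so that it says which confidence limit is compared with 3.5%, in which direction (SPD minus SDD), and whether a success stop, a harm stop or both are intended.
2. Add a non-binding guideline: if at a yearly look the lower limit of the 95% CI for SPD minus SDD is above 0 for recurrence, or for morbidity including deaths, the statistician refers the trial to the sponsor and ethics committee for a decision.
3. State the planned number and timing of the looks.

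The harm guideline needs no alpha adjustment. Any success stop that is kept is a separate matter for error control.

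The cost is one or two sentences for the rule and no new analyses beyond counting deaths within morbidity. The downside is unneeded referral when the arms are equal: about 1% for recurrence alone, and a few percent once morbidity and deaths are included, depending on their rates and the number of looks. Setting the trigger at 0 rather than at +3.5% is a choice; the higher value would give fewer referrals in both directions of error.

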### Ethical Issues

This study was approved by the local ethics committee (EKNZ, Basel, Switzerland, AG2013/001). The trial is conducted within the International Conference of Harmonization of Technical Requirements for Registration of Pharmaceuticals for Human Use Good Clinical Practice guidelines and the principles of the Declaration of Helsinki and is registered in the clinical study database ClinicalTrials.gov (NCT01869855).

## Results

The study is a currently ongoing study in two neurosurgical centers: Kantonsspital Aarau and University Hospital of Basel. Enrollment began in April 2013. We expect all study-related activities to be completed by the end of 2016 or beginning of 2017.

## Discussion

To date, evidence-based recommendations concerning the operative and postoperative treatment of cSDH are sparse. Most recommendations are based on observational or retrospective studies and some meta-analyses leading to class II or III recommendations [3]. For the surgical management of cSDH only one randomized controlled trial (RCT) exists, providing grade I evidence and showing that the intraoperative insertion of a drain after the completion of a burr-hole trepanation reduces the recurrence rates of cSDH significantly [2]. Further RCTs investigating and scrutinizing the standard treatment of cSDH are warranted, first and foremost due to the fact of a steady increase in the incidence of cSDH as a result of prolonged life expectancy [2,3]. With this multicenter RCT, we intend to provide grade I evidence (and class I recommendations) to an additional aspect in the surgical treatment of cSDH, namely the ideal and safest localization of an intraoperative drain. In our opinion this RCT will have great impact on the surgical management of patients presenting with this frequent condition. We hope that this clinical study will contribute to the important goal of evidence-based treatment of cSDH.

